#### Mitochondrial Measurements

Cardiolipin species will be measured in the peripheral blood mononuclear cell (PBMC) samples. PBMC cardiolipin fatty acyl molecular species mass will be quantified using electrospray ionization-mass spectrometry coupled to high-performance liquid chromatography as previously described [55,56].

#### Biochemical Markers

Glycated hemoglobin was measured using a finger stick. Erythrocyte and PBMC fatty acids will be analyzed. PBMC lipids will be extracted using methanol and chloroform (1:2 v/v) [57] and methylated using 5% hydrochloric acid in methanol [58] as previously described [59]. Erythrocyte fatty acid methyl esters will be prepared using 14% boron trifluoride in methanol and hexane [60] as previously described [61,62]. Gas chromatography with a 30-m Omegawax TM 320 fused silica capillary column (Supelco) will be used to analyze the fatty acid methyl esters. Standards for fatty acid methyl esters (Matreya, LLC and Nu-Check Prep Inc) will be used to determine retention times of fatty acids in the samples as previously described [63].

From blood collected at fasting and postprandial time points, lipid panels were measured at the OSU Wexner Medical Center Hospital Lab. Glucose will be measured using the Glucose Autokit (FUJIFILM Healthcare Americas Corporation), and insulin levels will be measured using the Meso Scale Diagnostics kit. Fasting glucose and insulin levels will be used to calculate estimated insulin resistance using the homeostatic model assessment of insulin resistance [64]. Markers of inflammation, including fasting and postprandial tumor necrosis factor alpha, tumor necrosis factor receptor 2, C-reactive protein, interleukin-6, and soluble intercellular adhesion molecule-1, will be measured at weeks 0 and 5. Fasting soluble CD14, oxidized low-density lipoprotein, and lipopolysaccharide binding protein will also be measured. Tumor necrosis factor α, tumor necrosis factor receptor 2, soluble intercellular adhesion molecule-1, C-reactive protein, interleukin-6, and lipopolysaccharide binding protein will be measured using a highly sensitive Meso Scale Diagnostics kit, and soluble CD14 and oxidized low-density lipoprotein will be measured by ELISA kits (R&D Systems and Mercodia, respectively). Lipopolysaccharide will be measured using Kinetic-QCL, Kinetic Chromogenic LAL Assay, or ELISA LifeSpan BioSciences. Markers of oxidative stress, 4-hydroxynonenal and malondialdehyde, will also be measured by multiplex methods as previously reported [54,65-68].

#### Questionnaires and Recalls

At the first study visit, participants were asked to complete the Baseline Questionnaire, a descriptive questionnaire asking about age, gender, sex, race, ethnicity, and health status. At the beginning of each intervention period, participants were asked to complete the Pittsburgh Sleep Quality Index [69] to capture sleep quality and disturbances, an Omega-3 Fatty Acid Checklist to determine omega-3 fat intake [70], and the Center for Epidemiologic Studies Depression Scale to assess depressive symptoms.

To measure dietary intake before enrollment in this study, participants completed the Diet History Questionnaire III, a food frequency questionnaire developed by the National Cancer Institute staff [71,72]. During this study, participants completed 24-hour dietary recalls, using the Automated Self-Administered 24-Hour Dietary Assessment Tool (version 2022 and 2024), developed by the National Cancer Institute. To assess changes in physical activity, 24-hour recalls were completed using the Activities Completed Over Time in 24 Hours, a web-based physical activity recall tool offered by the National Institutes of Health National Cancer Institute [73-75].

### Sample Size

The primary outcome used in sample size calculation was the postprandial cognitive test score from the NIHTB-CB. Based on our previous study [22], we obtained the SD (11.0) of the difference in postprandial cognitive test score between the unsaturated fat meal and the saturated fat meal. We had 80% power with 78 participants to detect a difference of 3.5 in postprandial cognitive test score between the control and the walnut group using a 2-sided paired *t* test with a type I error of 0.05.

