### Recruitment

A total of 78 adults with SCI were planned to be recruited from the central Ohio area. Inclusion and exclusion criteria are reported in Textbox 1. Study flyers were placed around the OSU campus and off-campus sites that include community centers, libraries, restaurants, and coffee shops. Additionally, study flyers were distributed to outpatient medical clinics in the Columbus, Ohio area. Potential participants were sent information about this study through The Ohio State Wexner Medical Center’s MyChart, and those who agreed to release their information to the research team were prescreened for eligibility. Radio advertisements were placed to reach potential participants outside of the OSU community. Recruitment for this study included or was carried out via ResearchMatch, a national health volunteer registry that was created by several academic institutions and supported by the US National Institutes of Health as part of the Clinical Translational Science Award program. ResearchMatch has a large population of volunteers who have consented to be contacted by researchers about health studies for which they may be eligible.

Inclusion and exclusion criteria.

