### Statistical Analysis

Postprandial cognitive test scores will be compared between the control and walnut group using a 2-sided paired *t* test to account for the cross-over design. To further adjust for covariates, a linear mixed effect model with subject-specific random intercept will be fit on postprandial test score with the following covariates: study group, preprandial test score at week 0 and 6, BMI, age, sex, education level, and depression score. The regression coefficient of this study’s group will be the adjusted difference in postprandial test score between this study’s groups. Potential carryover of treatment effects from the first treatment period to the second period will be assessed by including an interaction between treatment and period in the mixed-effect models. Significant interaction indicates the existence of a carryover effect, in which case we will only use data from the first treatment period to evaluate the treatment effect using a 2-sample *t* test and linear regression models. Analyses for the primary hypothesis will use participants who completed the entire study and will be based on an intention-to-treat principle, regardless of compliance and study group crossover. Sensitivity analyses will be conducted with multiple imputation on missing values for participants who do not complete the entire study. A linear mixed effect model with subject-specific random intercept will be fit on preprandial test score at week 1 and 6 with the following covariates: study group, preprandial test score at day 0 and 35, BMI, age, sex, and education level. The regression coefficient of this study’s group will be the adjusted difference in preprandial test score after a 7-day intervention between study groups. A linear mixed effect model with subject-specific random intercept will be fit on postprandial test score at weeks 0 and 5 with the following covariates: change in plasma sum of ALA+LA during 7-day intervention, BMI, age, sex, and education level. The regression coefficient of plasma sum of ALA+LA will measure the adjusted correlation between postprandial test score and change in plasma sum of ALA+LA.

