### Ethical Considerations

Review and approval for this study and all procedures were obtained from the OSU Institutional Review Board on April 24, 2023 (2023H0111). All interested potential participants were provided verbal and written information about this study, including a copy of the consent form. Potential participants had the opportunity to ask questions and be provided as much time as necessary to review the consent form and consider participating. Informed consent was obtained from all participants. Participants were compensated up to US $200 for participation in this study, where those who discontinued early received a prorated amount. Efforts were made to protect the privacy of this study’s participants, such as deidentifying participant information and limiting interactions with participants to essential study team members.

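### The stated 80% power holds only if all 78 recruited participants complete, because the recruitment target equals the number of pairs to be analysed

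*Protocol article*

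**What the plan says.** The Sample Size section of the protocol article takes its variability from an earlier study by the same group: "we obtained the SD (11.0) of the difference in postprandial cognitive test score between the unsaturated fat meal and the saturated fat meal". It then states "We had 80% power with 78 participants to detect a difference of 3.5 in postprandial cognitive test score", "using a 2-sided paired *t* test with a type I error of 0.05".

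Three other places bear on what the 78 means:

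- **Recruitment:** "A total of 78 adults with SCI were planned to be recruited from the central Ohio area".
- **Statistical Analysis:** "Analyses for the primary hypothesis will use participants who completed the entire study". Multiple imputation for participants who do not complete is planned, but only as a sensitivity analysis.
- **Ethical Considerations:** on compensation, "those who discontinued early received a prorated amount".

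The article gives no expected dropout rate, no larger recruitment target and no replacement rule.

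**The concern.** A paired t test uses only participants who contribute both postprandial scores. If 78 is the number of pairs needed, 78 is also the number of completers needed. Recruiting exactly 78 then leaves nothing for loss.

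The schedule gives some opportunity for loss. Participants enter at the week –1 visit, before the run-in and before randomization. They then have two one-week periods separated by a 4-week washout, with meal-challenge visits that include hourly measurements for 5 hours. The article makes provision for non-completion in both its analysis and its payment rules, but the power statement does not.

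What is at stake is how the result is read. If the trial finds no difference, a reader will set that against 80% power for 3.5 points. With fewer than 78 pairs, and the planning SD as stated, the trial's sensitivity was lower than that.

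**Working it through.** **Inputs, all from the Sample Size section unless noted.** Two-sided α = 0.05 (z = 1.960); power 80% (z = 0.842); mean paired difference δ = 3.5; SD of the paired difference = 11.0; planned recruitment 78 (Recruitment section).

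**Step 1: reproduce the stated figure (normal approximation).**

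n = [SD × (1.960 + 0.842) / δ]² = [11.0 × 2.802 / 3.5]² = 77.5, rounded up to 78.

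Power at 78: δ / (SD/√n) = 3.5 / (11.0/√78) = 2.810, and Φ(2.810 − 1.960) = 80.2%.

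The plan's figure is reproduced.

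**Step 2: exact power of the named test.** With a noncentral t distribution, noncentrality 3.5/(11.0/√n) and n − 1 degrees of freedom:

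- n = 78 gives 79.2%.
- n = 79 gives 79.8%.
- n = 80 gives 80.3%, the smallest n that reaches 80%.

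The gap between 80.2% and 79.2% at 78 is the normal approximation against the exact t, nothing more. Neither calculation leaves slack: at 77 pairs power is 79.7% (normal) or 78.7% (exact).

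**Step 3: recruit 78 and analyse completers only.** The article gives no dropout rate, so the losses below are assumptions. Completers are 78 × (1 − loss), rounded to a whole number.

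| Assumed loss | Completers | Exact power for 3.5 points | Difference detectable with 80% power |
|---|---|---|---|
| 0% | 78 | 79.2% | 3.53 |
| 5% | 74 | 77.1% | 3.63 |
| 10% | 70 | 74.7% | 3.74 |
| 15% | 66 | 72.1% | 3.85 |
| 20% | 62 | 69.4% | 3.98 |

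**Step 4: which participants count.** The Study Timeline section places the two postprandial cognitive tests at weeks 0 and 5, while the last visit is week 6. The primary set is defined by completing the entire study. As worded, a participant with both postprandial scores who misses week 6 is also excluded. The number in the primary set can therefore be smaller than the number of available pairs, and it is the relevant n for the power statement.

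**The case against.** The strongest reply has four parts.

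- **The power sentence is true as written.** It is conditional on 78 participants and reproduces. This stands. A reader might infer an arithmetic error from the 79.2% exact value, but a difference of about one point between two standard methods is not an error.
- **Nothing shows that loss occurred.** Prorated payment and a multiple-imputation sensitivity analysis are routine provisions. The abstract says 78 adults consumed the snacks, which could mean 78 treated. A full protocol, not shown here, could hold an allowance. This stands in part. A reader might infer that the trial was in fact underpowered, but the article reports no dropout count or rate and so does not support that. It does, however, state both numbers itself: 78 planned for recruitment and 78 for power. The abstract does not say that 78 completed both periods.
- **The 80% is not a strict upper limit.** The SD is borrowed from an earlier study, which the Discussion describes as done in women, with meals based on dietary oils. Required n scales with SD², so a true SD of about 10.4 (11.0 × √0.9) would offset a 10% loss, while a larger SD would lower power with no loss at all. The covariate-adjusted mixed model may also gain precision. This stands: 80% is a planning value, and the point concerns only the assumption attached to it.
- **Recruitment is over, and a null result is read from its confidence interval.** Both are right. The remedy is therefore confined to wording and reporting.

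**Conclusion.** The point holds as a matter of stated assumptions. The 80% is correctly computed for 78 analysed pairs, but the article recruits 78, analyses completers and provides for non-completion. Given the planning values (SD 11.0, difference 3.5) and the unadjusted paired t test, any loss puts power below the stated figure.

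The size is modest at low attrition. Relative to 79.2% at full completion, exact power falls by about 2 points at 5% loss, 4.5 points at 10% and 7 points at 15%. The difference detectable with 80% power moves from about 3.5 to 3.6, 3.7 and 3.9 points. These loss rates are assumptions, and the actual loss cannot be determined from the article. The matter deserves correction in the text but does not threaten the validity of the comparison.

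**What to change.** In the Sample Size section, state that about 80% power (79% by the exact paired t test) assumes 78 analysed pairs and no attrition.

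Then give the power for 3.5 points, and the difference detectable with 80% power, at the number actually in the primary analysis set. Count that set as the Statistical Analysis section defines it, that is, participants who completed the entire study, and not simply everyone with both postprandial scores.

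Interpret a null result from the confidence interval for the paired difference, which reflects the achieved number and SD, and not from the nominal 80%.

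The cost is a sentence or two and a slightly less favourable stated figure. The article reports that recruitment was completed by May 31, 2025, and projected the final visits for July 2025, so the analysed number should be known or nearly so. No further enrolment is proposed.

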### Statistical Analysis

Postprandial cognitive test scores will be compared between the control and walnut group using a 2-sided paired *t* test to account for the cross-over design. To further adjust for covariates, a linear mixed effect model with subject-specific random intercept will be fit on postprandial test score with the following covariates: study group, preprandial test score at week 0 and 6, BMI, age, sex, education level, and depression score. The regression coefficient of this study’s group will be the adjusted difference in postprandial test score between this study’s groups. Potential carryover of treatment effects from the first treatment period to the second period will be assessed by including an interaction between treatment and period in the mixed-effect models. Significant interaction indicates the existence of a carryover effect, in which case we will only use data from the first treatment period to evaluate the treatment effect using a 2-sample *t* test and linear regression models. Analyses for the primary hypothesis will use participants who completed the entire study and will be based on an intention-to-treat principle, regardless of compliance and study group crossover. Sensitivity analyses will be conducted with multiple imputation on missing values for participants who do not complete the entire study. A linear mixed effect model with subject-specific random intercept will be fit on preprandial test score at week 1 and 6 with the following covariates: study group, preprandial test score at day 0 and 35, BMI, age, sex, and education level. The regression coefficient of this study’s group will be the adjusted difference in preprandial test score after a 7-day intervention between study groups. A linear mixed effect model with subject-specific random intercept will be fit on postprandial test score at weeks 0 and 5 with the following covariates: change in plasma sum of ALA+LA during 7-day intervention, BMI, age, sex, and education level. The regression coefficient of plasma sum of ALA+LA will measure the adjusted correlation between postprandial test score and change in plasma sum of ALA+LA.

A linear mixed effect model with subject-specific random intercept will be fit on the change of endotoxemia during the 7-day intervention with the following covariates: study group, BMI, age, sex, and education level. The regression coefficient of this study’s group will be the adjusted difference in the reduction of endotoxemia between this study’s groups. β*-*diversity of the microbiome community at days 7 and 42 between all pairs of participants will be calculated using the Bray-Curtis dissimilarity measure. Nonmetric multidimensional scaling ordination will be computed, and nonmetric multidimensional scaling plots will be generated to visualize the difference in β-diversity between study groups. Permutation-based ANOVA will be used to compare the β-diversity between study groups. Operational taxonomic units (OTU) abundance will be compared between study groups using paired *t* tests for each OTU, and the *P* values will be adjusted by the Benjamini-Hochberg procedure [76] to control for false discovery rate. A linear mixed effect model with subject-specific random intercept will be fit on postprandial test score with the following covariates: change of endotoxemia during the 7-day intervention, change of OTU abundance during the 7-day intervention, BMI, age, sex, and education level. As the number of OTUs will be very large, exceeding the sample size, a LASSO (Least Absolute Shrinkage and Selection Operator) penalty [77] will be included in the regression model to select significant covariates.

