**Figure 1 figure1:**
[figure not shown]
Study timeline.

At the beginning of each intervention period (weeks 0 and 5), participants reported to the Clinical Research Center on the OSU campus. At the Clinical Research Center, weight, vitals, and waist circumference were measured, sleep and diet questionnaires were answered, fasting indirect calorimetry was completed, a fasting blood draw was collected, and the meal challenge was administered with subsequent blood draws and indirect calorimetry measurements performed hourly for 5 hours. Additionally, cognitive function was measured both fasting and at 5 hours after the meal challenge, and any updates to medications and supplements were recorded. Each intervention period lasted 1 week and concluded with a study visit (week 1 and week 6). At the week 1 and week 6 visits, weight, vitals, and waist circumference were measured. A fasting blood draw was collected, cognitive function was measured, and updates to medications and supplements were obtained. There was a 4-week washout period between intervention periods. Figure 2 describes the measurements and information collected at each study visit. Participants were supplied with enough study snacks to consume 1 study snack per day until their next study visit. No study snacks were consumed during the washout period. At study visits, this study’s team verbally asked participants about adherence to consuming 1 study snack per day, changes to diet or activity, and changes to medications or supplements.

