### Outcomes

#### Cognitive Function

The primary outcome of the EFFECT study is the difference in postprandial cognitive score between control and walnut interventions. Additionally, the difference in change of premeal score at the start and end of the intervention period between the control and walnut interventions will be analyzed. To assess cognitive function, the National Institutes of Health Toolbox for the Assessment of Neurological and Behavioral Function Cognitive Battery (NIHTB-CB) was used, specifically the fluid cognition battery. The tests are fully automated and administered via an iPad (Apple Inc) with consistent program-derived instructions. Minimal practice effects and no floor or ceiling effects are seen with the NIHTB-CB [48-50].

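### The only powered comparison for the primary outcome, a paired t test, leaves out the fasting score taken at the same visit, and no analysis is named as the deciding one

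*Protocol article*

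**What the plan says.** All places are in the Methods of the protocol article.

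- **Cognitive Function (Outcomes):** "The primary outcome of the EFFECT study is the difference in postprandial cognitive score between control and walnut interventions".
- **Sample Size:** the input is a previous study, from which "we obtained the SD (11.0) of the difference in postprandial cognitive test score between the unsaturated fat meal and the saturated fat meal". The claim is "We had 80% power with 78 participants to detect a difference of 3.5 in postprandial cognitive test score", for a 2-sided paired t test at a type I error of 0.05.
- **Statistical Analysis:** the first comparison is "Postprandial cognitive test scores will be compared between the control and walnut group using a 2-sided paired" t test. The next sentence adds, as a further adjustment, a mixed model on the postprandial score with a random intercept per participant. Its covariates are study group, preprandial score at weeks 0 and 6, BMI, age, sex, education and depression score. The section later refers to analyses for the primary hypothesis in the plural and ranks none of them.
- **Study Timeline:** at the start of each intervention period, weeks 0 and 5, "cognitive function was measured both fasting and at 5 hours after the meal challenge". Week 6 is the visit that closes the second intervention week.

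**The concern.** Each postprandial score has its own baseline, measured the same day before the meal. Pairing two postprandial scores removes stable differences between people. It does not remove differences between two visits of the same person, such as sleep, mood or form on the day, which can move the fasting and 5-hour scores of one visit together. The fasting score measures that shared part directly. Because it is taken before the challenge meal, adjusting for it is valid.

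The test that carries the stated power does not use this information. The model that does use a preprandial score is placed second, and as printed it takes the wrong visit in the second period. Read literally, no stated comparison of the two snacks adjusts the week 5 postprandial score for the week 5 fasting score.

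Two things are at stake: some precision on the primary comparison, and a clear rule for which result counts if the adjusted and unadjusted analyses differ.

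**Working it through.** **Inputs.** From Sample Size: SD of the within-person postprandial difference 11.0, difference 3.5, n = 78, two-sided alpha 0.05, paired test. Assumed: rho, the correlation between the walnut-minus-control difference in fasting score and the same difference in postprandial score. The article does not give rho, so a range is shown.

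**Step 1: reproduce the plan's figure.**

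n = ((1.960 + 0.842) × 11.0 / 3.5)² = 8.805² = 77.5, rounded up to 78.

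Power at n = 78 by the normal approximation is 80.2%. With the noncentral t distribution (noncentrality 3.5 × √78 / 11.0 = 2.81, 77 df) it is 79.2%. The stated 80% with 78 participants is therefore right for the test it names.

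**Step 2: adjust for the fasting difference.** Regress the within-person postprandial difference on the within-person fasting difference and take the intercept as the effect:

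residual SD = 11.0 × √(1 − rho²); noncentrality = 3.5 × √78 / residual SD; df = 76.

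| rho | Residual SD | Power, n = 78 | Gain over 79.2% (points) | Difference detectable at 80% power |
|---|---|---|---|---|
| 0 | 11.00 | 79.2% | −0.01 | 3.53 |
| 0.1 | 10.94 | 79.6% | 0.4 | 3.52 |
| 0.2 | 10.78 | 80.8% | 1.6 | 3.46 |
| 0.3 | 10.49 | 82.9% | 3.6 | 3.37 |
| 0.4 | 10.08 | 85.7% | 6.5 | 3.24 |
| 0.5 | 9.53 | 89.3% | 10.1 | 3.06 |

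A further degree of freedom for a period term brings the loss at rho 0 to about 0.03 points.

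**Step 3: check by simulation** (20,000 trials per rho for power, 10,000 for type I error). Adjusted power was 82.7% at rho 0.3 and 89.1% at rho 0.5, against 79% to 80% for the paired t test. Type I error was about 5% for both tests.

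**Step 4: is a plain change score a substitute?** With equal variances for the fasting and postprandial differences, the SD of the change-score difference is 11.0 × √(2(1 − rho)). Power is 65.0% at rho 0.3 and 79.2% at rho 0.5. A change score therefore loses power below rho 0.5, and regression adjustment does not.

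**Step 5: can the 80% be called conservative?** The primary analysis uses completers, and Sample Size states no dropout allowance. If 70 participants complete (an assumption), unadjusted power is 74.7%. Adjusted power is 75.1% at rho 0.1, 78.6% at 0.3 and 85.8% at 0.5. Whether the adjusted analysis exceeds 80% thus depends on both rho and the number of completers.

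**The case against.** The strongest reply is that the plan already adjusts. The mixed model follows the t test immediately, is fitted to the same postprandial score and includes a preprandial score. No sentence makes the t test the sole deciding analysis. This stands. A reader might infer from the order of the text and from the sample size that the unadjusted test alone settles the hypothesis, but the article does not say so. The fasting score is missing from the powered test, not from the plan. What remains is that no analysis is designated and that the adjusted model names the wrong second visit. The latter looks like a slip, because the 7-day model in the same section uses days 0 and 35, and day 35 is week 5.

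Second, the paired t test is valid, matches the stated outcome and has the power claimed for it. This also stands. The gain from adjustment is efficiency only. A reader might infer that a chance difference between walnut-day and control-day fasting scores biases the paired test. Under randomised order it does not; that variation is already in the standard error.

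Third, rho is unknown and could be low. Pairing has already removed stable differences, and the design limits day-to-day variation through the overnight fast, the food provided the day before and the restrictions on alcohol, exercise and medication. The article also reports minimal practice effects for the battery. At rho 0.2 or below the gain is under 2 points, so a large loss of power cannot be asserted.

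Fourth, the change would come late. Recruitment was completed by the end of May 2025, final visits were projected for July 2025, and the research team is not blinded. This does not remove the point, but it means that the choice must be fixed and documented before outcome data are analysed.

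**Conclusion.** The point holds as a modest improvement and a needed clarification, not as an error in the sample size. The only powered and first-named comparison leaves out a same-visit baseline that is collected anyway. The follow-on model that could use this baseline cites week 6 where the second challenge is at week 5, and nothing says which analysis decides.

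Under the plan's own inputs and all 78 pairs, adjustment adds from 0.4 points of power at rho 0.1 to 10.1 points at rho 0.5. The worst case is a loss of a few hundredths of a point. These figures rest on an assumed rho and on the planning SD of 11.0 applying in this trial.

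**What to change.** Before outcome data are analysed, name one fasting-adjusted within-person analysis as primary. Either of two forms would do:

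1. the planned mixed model, with each challenge visit's own fasting score (weeks 0 and 5 in place of weeks 0 and 6) and a period term; or
2. a regression of each participant's walnut-minus-control postprandial difference on the same difference in fasting score, with a term for sequence to carry the period effect.

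Keep the unadjusted paired t test as a sensitivity analysis. State that the 80% power with 78 participants was computed for that unadjusted test, and do not describe it as conservative.

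The cost is a few sentences in the analysis section, a dated record of the change because the article is already published, and one or two residual degrees of freedom. No new data are needed.

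### Neither the primary paired t test nor the listed mixed model has a period main effect; the likely cost is a small loss of power, and bias arises only if completers are unbalanced by sequence

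*Protocol article*

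**What the plan says.** The Sample Size section bases the trial on the difference in postprandial score "between the control and the walnut group using a 2-sided paired" t test. It states: "We had 80% power with 78 participants to detect a difference of 3.5 in postprandial cognitive test score". The SD comes from an earlier study by the same group: "we obtained the SD (11.0) of the difference in postprandial cognitive test score".

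The Statistical Analysis section repeats the choice for the primary comparison: "Postprandial cognitive test scores will be compared between the control and walnut group using a 2-sided paired" t test, which it presents as the way the crossover is accounted for. A random-intercept model then gives an adjusted difference. Its covariates are "study group, preprandial test score at week 0 and 6, BMI, age, sex, education level, and depression score". Neither period nor sequence is among them. Period is named once, inside an interaction with treatment that tests for carryover. If that interaction is significant, only first-period data are used. The primary analysis is restricted to people who completed the whole study, with multiple imputation as a sensitivity analysis.

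On timing, the Study Timeline section says that at weeks 0 and 5 "cognitive function was measured both fasting and at 5 hours after the meal challenge", and it adds one further test at each of weeks 1 and 6. On practice, the Cognitive Function section states: "Minimal practice effects and no floor or ceiling effects are seen with the NIHTB-CB".

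**The concern.** A paired t test removes differences between people. It does not remove a difference between the first and second period that everyone shares. Such a shift adds to the walnut-minus-control difference in people who take walnuts second and subtracts from it in people who take walnuts first. The test then counts it as random noise. If the two sequences contribute unequal numbers, part of it also stays in the estimate.

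Two features of the design make a shift possible. First, the battery is repeated, so the two primary measurements are not at the same point in the series of tests. Second, the lead-in differs: the first meal challenge follows a week of daily run-in snacks, the second follows four weeks without study snacks.

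At stake are a little power for the primary comparison and, if dropout differs by sequence, a modest distortion of the treatment difference.

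**Working it through.** **Exposure count.** The Study Timeline section gives: week 0 fasting (1), week 0 postprandial (2), week 1 (3), week 5 fasting (4), week 5 postprandial (5), week 6 (6). It lists no battery test at week –1. The primary measurements are therefore exposures 2 and 5. Figure 2, the measurement timeline, is not shown, so this rests on the text.

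**The plan's own figure.** Inputs from Sample Size: difference 3.5, SD of the difference 11.0, N = 78, two-sided "test with a type I error of 0.05".
- Normal approximation: n = (11.0 × (1.960 + 0.842) / 3.5)² = 77.5, rounded up to 78; power 80.2%.
- Noncentral t with 77 df: power 79.2%.

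The stated 80% is reproduced.

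**Model with a period shift.** Let π be the period-2 minus period-1 shift and τ the treatment effect. Person i's walnut-minus-control difference is D = τ + sπ + e, with s = +1 if walnuts come second, s = −1 if they come first, and SD(e) = 11.0. The document gives no value for π, so 0 to 5 points is an assumed range. Equal sequences (39:39) are also assumed; blocks of 2 and 4 make a near-equal split likely at randomisation.

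**Case A: 11.0 excludes period variation (assumption), 39:39.** The SD that the paired t test sees is about √(121 + π²). The mean of D still has variance 121/78, because the +π and −π cancel. The test statistic is thus a normal variable over an inflated SD: the sum of squares divided by 121 is noncentral chi-square with 77 df and noncentrality 78π²/121. Integrating over that distribution gives:

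| π (points) | SD seen, √(121 + π²) | Power, paired t | Type I error, paired t | Power with period term (76 df) |
|---|---|---|---|---|
| 0 | 11.0 | 79.2% | 5.0% | 79.2% |
| 1 | 11.05 | 79.0% | 4.9% | 79.2% |
| 2 | 11.2 | 78.3% | 4.6% | 79.2% |
| 3 | 11.4 | 77.1% | 4.2% | 79.2% |
| 5 | 12.1 | 73.2% | 3.1% | 79.2% |

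Simulation with 40,000 trials per setting agrees: 77.5% and 73.0% power at π = 3 and 5, with null rejection of 4.1% and 3.1%. Putting the inflated SD into the ordinary noncentral t formula gives lower power (76.3% and 71.3%). That overstates the loss, because it also inflates the variance of the mean.

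**Case B: 11.0 already includes period variation.** The unadjusted power is then the planned 79.2%. A period term leaves a residual SD of √(121 − π²), which is 10.6 at π = 3 and 9.8 at π = 5, and power rises to about 82% and 88%.

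**Bias.** With n₁ completers taking walnuts second and n₂ taking them first, the mean of D is τ + π(n₁ − n₂)/(n₁ + n₂).
- 39:39: zero for any π.
- 38:32 (assumed; no dropout figure is given): π × 6/70 = 0.09, 0.17, 0.26 and 0.43 points at π = 1, 2, 3 and 5, which is 2%, 5%, 7% and 12% of 3.5.
- With a period term: zero.

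**The case against.** The strongest reply is the plan's own statement that practice effects are minimal. Shifts of 3 to 5 points are 86% to 143% of the 3.5-point target difference and sit badly with that statement; at 1 or 2 points the loss of power is one point or less. This stands, and it is why the low end of the range belongs in the table. It does not remove the point: minimal is not zero, no figure is given, and the statement does not cover the different lead-in to the two periods.

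The SD of 11.0 may be a raw SD from an earlier two-meal comparison that already contains period variation. That also stands. In that case the planned power is not reduced, and a period term is a gain and not a repair.

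The mixed model's preprandial covariate could absorb part of a practice shift, since exposure 1 precedes 2 and exposure 4 precedes 5. This is fair, and the figures above apply to the paired t test only. The covariate as written, however, pairs weeks 0 and 6, while the second meal challenge is at week 5, so the same-visit adjustment is not clearly in place.

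The carryover model does involve period, and in ordinary practice an interaction is fitted with its main effects. But it serves as a diagnostic. If the interaction is not significant, the reported estimates are those without period; if it is significant, only period 1 is used.

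Multiple imputation for non-completers would tend to restore the randomised balance of sequences, but only as a sensitivity analysis.

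A reader might infer that the primary result is materially biased or that false positives are inflated. The documents do not support this. With balanced sequences the test is unbiased and errs on the conservative side, and no dropout imbalance is reported.

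**Conclusion.** The omission is a stated choice, visible in the Statistical Analysis section, and not a detail left to an unseen analysis plan. Its direction is certain; its size is modest and depends on a shift that the article does not quantify. If 11.0 excludes period variation and sequences are equal, power falls by about 0.2, 2 and 6 percentage points at shifts of 1, 3 and 5 points, with type I error at or below 5%. If 11.0 includes period variation, planned power holds and precision is left unused. Bias is zero with balanced completers, and 0.09 to 0.43 points in the assumed 38:32 example for shifts of 1 to 5 points.

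The other treatment-comparison mixed models, for the 1-week cognitive score and for the change in endotoxemia, also list no period term. No size is claimed for them. For endotoxemia the reason to add one is general differences between periods; learning of a test cannot apply to a blood marker.

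**What to change.** Before analysis, and by a dated change, name one period-adjusted crossover comparison as primary. There are two candidates, and they are different estimators, so the plan should choose one:

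1. A two-sample t test comparing within-person period differences between the two sequences. For complete pairs this is equivalent to a random-intercept model with study group and period only.
2. A mixed model with study group, period and the same-visit preprandial score (weeks 0 and 5). The covariate makes this distinct from option 1.

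Add period as a fixed effect to the other two-period treatment-comparison mixed models. Keep the paired t test as a supportive analysis, and report completers by sequence so that a reader can judge the bias term.

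The statistical cost is one degree of freedom; at 39:39 power is 79.2% with or without it when there is no shift. The procedural cost is a documented, justified change. Recruitment is complete and the research team is not blinded, so the date and reason should be recorded before outcome data are compared by snack.

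Suggested wording: *The primary comparison of postprandial score will adjust for period by comparing within-person period differences between the two sequences; a paired t test will be reported as supportive.*
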